#### Health economic analysis

We will assess the feasibility of collecting the data required for a health economic analysis. This will include detailed descriptive statistics on completion of the health service use telephone interviews, which will include social care costs and costs incurred by dyads. Health service use costs will include both those from falls (both intervention arms) and in relation to injury while carrying out Tai Chi. The total cost of providing the intervention to each patient will be estimated from weekly records collected from the Tai Chi instructor and in relation to: (a) the average cost of hire of the building for the classes (taken from the costs incurred in this study), and (b) the instructor’s time spent delivering the intervention as a function of hourly rate. Health service use on falls will be calculated in relation to presentation to the GP, out of hours, or ED. We will also explore cost effectiveness results for PWD and their carers between arms in terms of incremental cost per change in quality of life. All health economic analyses will be presented descriptively in terms of completion (missing data) and outcomes (e.g. mean and SD in relation to baseline and follow-up), as the study has not been powered to conduct a full health economic analysis, which is reserved for the subsequent definitive trial.

#### Safety monitoring

The monitoring of participants’ safety will be achieved primarily through weekly telephone contacts between unblinded researchers and dyads and dyads’ weekly record keeping. Participation in the trial is considered to be of relatively low risk and participants are not expected to be harmed as a result of taking part. As such, the recording and reporting of adverse events will be limited to adverse events related to the Tai Chi intervention and balance test assessments. No treatment will be provided to participants in addition to NHS usual care.

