Falls measurements will be collected prospectively from baseline until six months post-baseline. These include the number of falls by PWD (count data), the proportion of PWD who have fallen (binary outcome measure), and number of injurious falls (count data). The collection of falls data is in accordance with recommendations made by the Prevention of Falls Network Europe (ProFaNE) [38]. In our trial, the definition of a fall is, “an unexpected event in which the participants come to rest on the ground, floor or lower level” [38]. Falls will be recorded by dyads daily using prospective monthly calendars and returned on a monthly basis by post for data entry. Where falls are reported by dyads or calendars are not returned, a researcher will conduct a telephone interview to collect further information about the fall/clarify missing data. Telephone calls will be conducted weekly with the PWD as recommended for falls data collection with PWD [39]. In addition, to ascertain the accuracy of different recall periods, telephone calls about fall incidents by the PWD will be made monthly with the PWD and every 3 months with the carer. Fall injury will be recorded by telephone interview when recording falls as described above, using an existing set of definitions for severity of injury ([11, 40], p.).

Within the intervention group only, data will be collected half-way through the intervention on a 5-item questionnaire to ask about the importance of features of the intervention such as enjoyment of the classes and confidence in being able to continue to do the home practice. At the end of the final home visit, all dyads will be asked to complete a brief structured exit interview that asks about their hypothetical willingness to pay for the Tai Chi intervention should it be offered in the future as part of routine NHS care. The researcher will also ask participants if there have been any significant changes during the trial to their medical status (e.g. medication usage or elective surgery), which may influence performance on the primary outcome.

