One subgroup analysis is pre-planned for the primary outcome variable (TUG). Fall history at baseline (had a fall or not in the past 12 months), which is also the variable used for minimization in addition to treatment condition, will be entered as an interaction term in a statistical model (intervention effect x effect modifier). Departures from the proposed analysis, for example due to poor recruitment, will be explained and justified in the main trial paper. Feasibility objectives will be addressed by estimating recruitment and attrition rates (with 95% confidence intervals) and falls data parameters (falls rate, proportion of fallers, and completeness of falls data) for a future sample size calculation. In addition, we will compare the frequency of falls reported by each of the individual methods of data collection and their combination to determine if the increased resource in collecting falls data weekly provides more accurate data.

Descriptive data from the structured exit interviews will be presented on hypothetical willingness to pay for the intervention and perceived changes to health (PWD and carer). Data on number of Tai Chi classes attended and adherence to home practice will be presented. To assess adherence to the intervention in the Tai Chi arm we will calculate: adherence to classes (i.e. x attended out of y possible) and adherence to home exercise (i.e. x minutes exercise out of y recommended). The following data will not be reported in the main trial outcome paper but will be included in further secondary analyses in relation to visual spatial cognitive functioning (statue task); comparison of the different methods of data collection on incidence of falls; qualitative data; and uptake and adherence to the intervention (whether the PWD or carer had done Tai Chi before, mean (SD) intention and perceived behavioural control to do Tai Chi, and intervention group responses to the questionnaire delivered half way through the intervention).

Given the short-term (6-month) follow-up, low-risk intervention being tested, and no planned interim analyses, there will be no data monitoring committee for the trial. The trial will only be stopped early if the intervention is considered to be directly causing undue harm to patients as independently considered by the trial steering committee and/or NHS Research Ethics Committee.

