#### Responsibilities of the trial steering committee (TSC)

The TSC will oversee the conduct and safety of the trial, ensuring that milestones are achieved and general scientific probity is maintained. The TSC will meet by teleconference on a bi-annual basis. The TSC will review progress against key milestones and reports of aggregate data (blinded) with a particular focus on adverse events. The TSC will be independently chaired and include independent members from the trial that represent expertise in statistics, clinical care of older people, relevant research knowledge and experience, and representation of older people with dementia and their informal carers.

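### Recording only related adverse events prevents a between-arm comparison of serious events other than falls of the person with dementia, and no clear by-arm view of falls is provided during the trial

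*Protocol article*

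**What the plan says.** All references are to the protocol article.

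- **Safety monitoring.** Safety is followed mainly through weekly telephone contact by researchers who know the allocation, and through the dyads' own records. On scope, "the recording and reporting of adverse events will be limited to adverse events related to the Tai Chi intervention and balance test assessments".
- **Statistical methods.** Because follow-up is short, the intervention low-risk and no interim analysis planned, "there will be no data monitoring committee for the trial". The stopping criterion is causal: "The trial will only be stopped early if the intervention is considered to be directly causing undue harm to patients". That judgement is left to either or both of two bodies, the steering committee and the ethics committee.
- **Responsibilities of the trial steering committee.** "The TSC will review progress against key milestones and reports of aggregate data (blinded) with a particular focus on adverse events". Also: "The TSC will meet by teleconference on a bi-annual basis".
- **Outcomes.** For people with dementia, falls, fallers and injurious falls are collected prospectively over six months by calendar and telephone, whatever their cause. Statistical methods then compares fall counts and the proportion of fallers between arms.

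**The concern.** The stopping criterion asks whether the intervention causes harm. The adverse-event rule filters on the answer to that question before anything is recorded. An event enters the data only once someone has attributed it to Tai Chi or to a balance test. In a population that the Background describes as falling more than twice as often as cognitively intact peers, a fall or injury some hours after home practice can look like any other. A single case then says little, and a comparison between arms is what separates intervention from background.

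Two things are at stake. For deaths, admissions, non-fall injuries and carer falls, the comparison is lost for good, because events not recorded during follow-up are hard to recover afterwards. For falls of the person with dementia the data exist, but the article does not say that those who judge harm will see them by arm while later class cohorts are still entering. The hazard is not remote: practice is standing, is chosen to challenge balance, and is done daily at home with an informal carer.

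**Working it through.** The safety sections give no figure to reproduce, so the check sets the sections side by side and adds one illustration.

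**Step 1. What each arm can contribute under the rules as written.**

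| Event | Tai Chi arm | Control arm | Between-arm comparison at the end |
|---|---|---|---|
| Event judged related to Tai Chi | recorded | none by construction (controls are asked not to take up Tai Chi) | not meaningful |
| Event related to a balance test | recorded | recorded | possible; baseline tests precede randomisation, so only the six-month visit counts |
| Falls of the person with dementia | recorded, any cause | recorded, any cause | yes (negative binomial and logistic models) |
| Injurious falls of the person with dementia | recorded, any cause | recorded, any cause | possible from the data |
| Fall-related GP, out-of-hours or emergency use | recorded | recorded | descriptive (Health economic analysis) |
| Deaths, admissions or non-fall injuries not judged related; carer falls not judged related | not described as recorded | not described as recorded | no |

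The exit interview asks about significant changes in medical status. It is a single question at the final visit, and it misses anyone who died or left before then. It does not replace event recording.

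**Step 2. The stopping criterion against the data supplied.** The steering committee and/or the ethics committee must judge causation. The adverse events described contain almost nothing from controls. No section says that falls or injurious falls are sent to either body by arm during the trial.

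**Step 3. What a pooled report would show, if the blinded aggregate reports are pooled.** With 1:1 allocation and equal follow-up, a rate ratio RR (Tai Chi to control) multiplies the pooled rate, relative to no effect, by

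(1 + RR) / 2.

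- RR = 1.5: (1 + 1.5) / 2 = 1.25, a 25% rise.
- RR = 2: (1 + 2) / 2 = 1.50, a 50% rise.

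The article gives no expected proportion of fallers, so assume 30% to 60% in controls, multiplied by 1.5 under Tai Chi:

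- Control 30%, Tai Chi 45%: pooled (30 + 45) / 2 = 37.5%.
- Control 40%, Tai Chi 60%: pooled (40 + 60) / 2 = 50%.
- Control 60%, Tai Chi 90%: pooled (60 + 90) / 2 = 75%.

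A pooled 50% arises equally from 40% against 60% and from 50% in both arms. The pooled figure alone cannot tell them apart.

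**Step 4. What separation by arm would add.** For two proportions at two-sided 5%, with n per arm and mean proportion p̄,

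power = Φ{ [ |p₂ − p₁| − 1.96 √(2 p̄(1 − p̄)/n) ] / √( [p₁(1 − p₁) + p₂(1 − p₂)]/n ) }.

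| Control | Tai Chi | n = 75 per arm | n = 37 per arm |
|---|---|---|---|
| 30% | 45% | 47% | 26% |
| 40% | 60% | 69% | 40% |
| 50% | 75% | 89% | 61% |
| 60% | 90% | 99% | 86% |

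For the first row with n = 75: [0.15 − 1.96 × √(2 × 0.375 × 0.625/75)] / √((0.21 + 0.2475)/75) = (0.15 − 0.155)/0.078 = −0.06, so power is 47%. The 75 per arm is the planned number randomised, and 37 stands for about half of it. No formal interim test is meant. The table shows only that arm-separated data carry information which a pooled count does not, and that this information is limited halfway through.

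**The case against.** The strongest reply has five parts.

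1. **Falls are not lost.** A reader might infer that falls and injuries go unrecorded unless attributed to Tai Chi. The Outcomes section contradicts this for people with dementia, and Health economic analysis adds fall-related service use in both arms. This stands, and confines the capture gap to the other serious events.
2. **The steering committee is not the only body.** One might read it as the sole body able to stop for harm, but Statistical methods also names the ethics committee. This stands. It does not close the gap, because no by-arm data are described for either.
3. **Blinded aggregate need not mean pooled.** It could mean tables with coded arms, much as the final results are first shown to the team with arm identity hidden. The article does not settle this, so it does not support saying that the committee cannot see a difference. It supports saying only that a by-arm view is not clearly provided. Step 3 depends on the pooled reading.
4. **Who judges relatedness is not stated.** One might infer that staff who know the arm decide it at collection. The article says only that unblinded researchers make the weekly contacts. The bias from filtering on relatedness does not need that inference.
5. **The article summarises a longer protocol, and the criterion concerns direct causation.** Report layouts and serious-event procedures may well be in the full document, so their absence is not criticised. The recording rule, however, is a stated restriction and not an omission. Case-by-case attribution is relevant to direct harm, but it cannot show an excess of events that look like background.

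Two smaller replies also have weight. Fall history over the past 12 months and past month gives a rough, retrospective reference for a pooled rate. Arm-separated tables in a trial of 150 dyads could also miss a true excess, as the 37-per-arm column shows.

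**Conclusion.** The point holds in two parts of different strength.

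- **Capture (firm).** As written, the rule leaves the control arm with almost no adverse events. Deaths, admissions, non-fall injuries and carer falls not judged related cannot be compared between arms at any stage. This rests on the stated rule and on no calculation. Deaths might surface as reasons for attrition, but the article does not say so.
- **Review during the trial (conditional).** Falls and injurious falls of people with dementia are available in both arms, but the article provides no clear by-arm view of them to those who judge harm. If the reports are pooled, a 50% excess appears as a 25% rise and a doubling as a 50% rise. If the arms are coded, this part reduces to a clarification.

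The documents do not support saying that harm from falls would go undetected altogether: falls are compared at the end. Nor do they show that the absence of a data monitoring committee is itself wrong, since reasons are given for it. The point merits a small amendment and casts no doubt on the primary analysis.

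**What to change.** 1. **Recording.** Record all serious adverse events in both arms, for the person with dementia and the carer, through the existing weekly contacts by unblinded researchers. Assess relatedness afterwards as a separate field, state who assesses it, and report the events by arm.
2. **Review.** State that the independent steering committee members receive falls, injurious falls and serious adverse events separated by arm at their existing twice-yearly meetings. Coded labels suffice. Say who prepares the table: the article describes the statistician as unblinded for the data export, so interim access needs its own sentence.
3. **Wording.** Say whether the blinded aggregate reports are pooled or coded by arm.

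**Cost.** There would be a few more events to log and verify, a definition of a serious event if the full protocol lacks one, and one extra table per meeting. Outcomes describes the weekly call as made with the person with dementia, so serious events will need confirmation from the carer. Asking about them after the falls questions would protect the planned comparison of falls-collection methods. The independent members would see arm-separated safety data. Blinding of outcome assessors need not change, because the weekly contacts are already made by unblinded researchers. No stopping threshold is proposed.

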#### Responsibilities of the trial steering committee (TSC)

The TSC will oversee the conduct and safety of the trial, ensuring that milestones are achieved and general scientific probity is maintained. The TSC will meet by teleconference on a bi-annual basis. The TSC will review progress against key milestones and reports of aggregate data (blinded) with a particular focus on adverse events. The TSC will be independently chaired and include independent members from the trial that represent expertise in statistics, clinical care of older people, relevant research knowledge and experience, and representation of older people with dementia and their informal carers.

### Ethics and dissemination

#### Access to data

Anonymised electronic records and paper copies of records will be open to inspection and monitoring from a recognised representative from either the Sponsor, Bournemouth University, the CTU, or the funder (National Institute for Health Research). The trial management group will have access to the full dataset. Other interested parties may make a formal request to access the electronic dataset, which will be approved / declined by the CI in accordance with the Data Management Plan that will detail management of access, sharing, and preservation of the data. Any use of the electronic data set must comply with the dissemination policy (see below) and be requested via Bournemouth University Library ([contact]) who will collaborate with the CI with regards to access. Non-digital data supporting this study will be stored by the corresponding author at Bournemouth University. Only electronic data will be shared with bona fide researchers intending to use the data for non-commercial research purposes, after an embargo period of approximately 24 months. Access to the following will be restricted to researchers who sign a confidentiality agreement and confirm their intention to use the data is for secondary data analysis for non-commercial research purposes using a Creative Commons licence: statistical analysis plan; where applicable, statistical code (for final analysis of primary outcome measure); and anonymised participant-level dataset and data documentation.

#### Dissemination policy

We intend to notify participants involved in the trial of the study findings through our annual public engagement events and a newsletter on study completion. We will disseminate to researchers and healthcare professionals through conference presentations and scientific journal publications, and the general public through our webpage for the trial (www.bournemouth.ac.uk/tai-chi). In all dissemination, no professional writers will be used. To establish authorship eligibility, we will use the uniform requirements for manuscripts submitted to biomedical journals established by the International Committee of Medical Journal Editors (ICMJE; www.icmje.org).

## Discussion

### Public and patient involvement (PPI)

PPI informed the development of the grant application for the trial. In particular, we held a small group discussion with two PWD and four carers (two carers were spouses and two were daughters of men with dementia). The idea of doing a Tai Chi intervention was presented to the group, with an explanation of Tai Chi provided by a qualified instructor. The group found the idea of a Tai Chi intervention appealing, and influenced the application in four ways: The inclusion of informal carers in dyads beyond partners / spouses; the provision of weekly classes for the whole 20-week course; the importance of ease of transport to each venue; and asking dyads about hypothetical willingness to pay for the intervention at the exit interview. Since the project began, a PPI advisory group of ten people (4 PWD, 5 spouses of PWD, and a daughter of a PWD) have inputted into the development of this trial protocol and continue to provide PPI input throughout the trial at regular intervals.

### Progress to date

At the time of submission, the trial is open to recruitment and the first dyad was recruited on June 7th, 2017. The title of the trial for the public is, “The TACIT Trial: TAi ChI for people with demenTia”. [name] is the contact for all public queries.

## Abbreviations

BBS: Berg Balance Scale
CI: Chief Investigator
ED: Emergency Department
ICECAP-O: ICEpop CAPability measure for Older people
Icon-FES: Iconographical Falls Efficacy Scale
M-ACE: Mini-Addenbrooke’s Cognitive Examination
NHS: National Health Service
PPI: Public and Patient Involvement
PWD: People with dementia
RCT: Randomised Control Trial
SD: Standard deviation
TSC: Trial Steering Committee
TUG: Timed Up and Go test
